**Study Design**

Each patient will be examined by at least five independent principal investigators. Investigator 1 will perform a basic oral examination using a clinical inspecting apparatus and X-ray, check all of the inclusion and exclusion criteria, and ensure that the informed consents are signed by the patients at the Registration Center. Next, Investigator 2 will perform the pre-surgical treatments, re-check the inclusion and exclusion criteria, and extract the tooth/teeth that will be subjected to cell isolation by Investigator 4. Investigator 2 will select no more than 2 teeth (from different regions) to be investigated in each patient. Following the collection of baseline data from the selected tooth/teeth by Investigator 3, Investigator 4 will culture the cells, make the cell products, and create an allocation table consisting of 2 cases per block that will be allocated to the Control group (Bio-oss® only) and Cell group (Bio-oss® and cell sheets). According to this allocation table, a label indicating the corresponding group will be attached to each tooth; thus, each tooth will be randomly assigned to one of the two treatment groups. The maximum number of teeth from one patient will be 2. Hence, if one tooth is allocated to the Control group, the other will be automatically assigned to the Cell group. However, if a patient only has one tooth chosen for investigation, it has a fair chance of being allocated to either group. Once a tooth is assigned to a group, it will be kept in a secure locked drawer inaccessible to all other study personnel. All of the patients will receive oral hygiene instructions, a tooth cleaning and basic dental therapies if needed, such as cavity filling and occlusal adjustment. The periodontal surgery will be performed 4-5 weeks after these pre-surgical treatments. When the oral condition and cell products are both ready for surgery, Investigator 4 will be asked to give the assigned implants (Bio-oss® only or a combination of Bio-oss® and cell sheets) to the physician (Investigator 5), who will then perform the surgery. This procedure ensures that the randomization is not influenced by the physicians taking part in this study. Investigator 4 will record the patients’ details and number the envelope assigned to each tooth. Investigator 3 will perform the follow-up study (data collection, safety assessment, etc.) of the patient, and the blind will not be broken until this clinical trial is completed.

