***Study Products***

Bio-Oss® and Bio-Guide® (Geistlich Pharma AG, Volhusen, Switzerland) and PDL cell sheets (cells obtained from a patient’s tooth/teeth; see inclusion criteria) will be produced at the Research and Development Center for Tissue Engineering (Fourth Military Medical University, [name]) using a standardized procedure (see section 5.1. cell products). Both transplants (Bio-oss® only or Bio-oss®/cell sheets) will be prepared (ready for immediate use) by the laboratory researchers, and Investigator 3, who will perform the follow-up study, will remain blinded to the treatment conditions.

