***Cell sheets***

To create the cell sheet, the PDLSCs will be digested by trypsin to obtain single cell suspensions and then inoculated on 6-well plates at 1×105 per well with L-ascorbic acid (vitamin C; VC, 30 μg/mL, Sigma) until confluent (approximately day 10). Next, we will observe changes in cell morphology and sheet-forming capacity. After a 10-day culture, white membranous substances will appear on the bottom of the wells. Before clinical application, the culture medium will be discarded, and the cell sheets will be rinsed twice with phosphate-buffered saline (PBS; Gibco). Next, the 0.2-µm CBB particulates will be distributed onto the surface of the cell sheets at a concentration of 0.25 g per well. The PDLSC cell sheets will then be rolled up to pack the Bio-oss® particulates for clinical treatment.

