**Statistics**

This study will be performed using a per-protocol analysis. In this analysis, all of the randomized teeth will receive at least one therapy, but teeth that do not receive treatment will be excluded (modified per-protocol analysis). The last-observation-carried-forward method will be used for the per-protocol analysis. The missing data points will be input into the post-baseline follow-up visits from the last observation available for each patient. For analysis, we will use SAS version 8.2 software (SAS Institute Inc., Cary, North Carolina, USA). The per-protocol set analysis will be performed for the primary outcome. The baseline between-group comparisons within age and clinical examination indices will be performed using independent group *t* tests. The between-group comparison of sex will be performed using Fisher’s exact probability test. The changes in clinical examination indices will be tested using a repeated-measures analysis of variance. The level of statistical significance will be set at *p*<0.05.

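### The surgeon receives the assigned, visibly different implant before operating, and untreated teeth are dropped: later disclosure would reduce, not remove, the room for bias

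*Protocol*

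**What the plan says.** **Sequence.** Study Design has Investigator 4 make the cell products, draw up the allocation table and hold the assignments. Once a tooth is assigned, the protocol says "it will be kept in a secure locked drawer inaccessible to all other study personnel". When the mouth and the product are ready, "Investigator 4 will be asked to give the assigned implants" "to the physician (Investigator 5), who will then perform the surgery".

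**Safeguard claimed.** The same section concludes: "This procedure ensures that the randomization is not influenced by the physicians taking part in this study".

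**Form of the implants.** Under Cell sheets, the test product is described thus: "The PDLSC cell sheets will then be rolled up to pack the Bio-oss® particulates for clinical treatment". The control is Bio-oss alone. Under Study Products, both transplants "will be prepared (ready for immediate use) by the laboratory researchers".

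**Who is blinded.** The protocol states blinding for the follow-up investigator (Study Products), the two radiograph readers (Efficacy assessment) and the patients (Discussion). It makes no such statement for the surgeon.

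**Analysis set.** The Statistics section expects every randomized tooth to receive at least one therapy, but adds that "teeth that do not receive treatment will be excluded (modified per-protocol analysis".

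**Allocation.** Investigator 4 will "create an allocation table consisting of 2 cases per block". A patient contributes at most two teeth, and the second automatically goes to the arm opposite the first.

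**The concern.** A surgeon cannot place a rolled cell sheet without noticing it, so some unblinding is unavoidable. The timing is not. As written, the arm can be known from the start of the operation, before the defect is exposed and the site prepared. Two things could then differ by arm: how thoroughly the site is prepared, and whether a tooth goes on to be grafted. The second matters because an ungrafted tooth leaves the analysis.

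Both would occur after randomization and before any outcome is read. Blinded radiograph readers cannot restore a missing tooth or undo unequal site preparation. With about 40 teeth in all, a few selective losses would be a noticeable share of one arm.

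**Working it through.** The protocol gives no standard deviation, target difference, power or expected number of untreated teeth, so there is no planned figure to reproduce. Three checks were made.

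**1. Order of events**
- Before handover: the assignment is locked away. Screening, tooth selection and baseline measurement are done by Investigators 1 to 3.
- Handover: the implant goes to the surgeon, who then operates.
- After handover: exposure, site preparation, grafting.
- The safeguard sentence concerns the randomization, that is, which arm a tooth is assigned to. It does not address the steps after handover or which teeth are kept in the analysis.

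**2. Size of selective loss (illustration)**

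Inputs: 40 teeth (Patients and enrolment), taken as 20 per arm. Assumed: independent teeth, unit SD, and *k* teeth lost from one arm, each 1 SD below that arm's mean.
- Shift of the arm's mean = *k*/(20 − *k*) SD. For *k* = 1: 1/19 = 0.053. For *k* = 2: 2/18 = 0.111.
- Standard error of the difference = √(2/20) = 0.316 SD.
- Ratios: 0.053/0.316 = 17% and 0.111/0.316 = 35%.

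A second illustration drops the *k* teeth with the worst prognosis in one arm. It assumes no true effect, a correlation between prognosis and outcome of 0.3 to 1.0, and a two-sided z-test at 0.05 (the protocol does not state sidedness):

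| Teeth dropped | Shift of the arm's mean (SD) | Type I error |
|---|---|---|
| 1 | 0.03 to 0.10 | 5.1% to 6.1% |
| 2 | 0.06 to 0.18 | 5.3% to 8.7% |
| 3 | 0.08 to 0.26 | 5.6% to 12.4% |

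**3. What later disclosure would leave**

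Inputs: about 30 patients, about 40 teeth, at most two teeth each, blocks of 2.
- Two-tooth patients: 40 − 30 = 10. One-tooth patients: 30 − 10 = 20.
- Within a block of 2, the first assignment fixes the second. Take each two-tooth patient as one block and pair the one-tooth patients. The fixed teeth are then 10 (second teeth) + 20/2 = 10 (second members of one-tooth blocks), in all 20 of 40, or 50%.
- A surgeon who remembers earlier assignments would know half and guess half of the rest: 0.5 × 1 + 0.5 × 0.5 = 75% correct. If the arm is visible at the present handover, it is known for every tooth.
- If both sites of a two-tooth patient are operated on in one session and prepared before either arm is disclosed, the first group of 10 drops out. That leaves 10 of 40, or 25%.

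**The case against.** **No treatability decision is described.** A reader might infer that the surgeon judges during the operation whether a tooth can be treated, and that teeth found untreatable are then removed. The protocol does not say so. Eligibility rests with Investigators 1 and 2, and the Statistics section speaks only of teeth that receive no treatment. Such teeth may be lost before surgery, for instance through withdrawal or lack of a usable cell product, and later disclosure would not affect those losses. This stands: the route through exclusion is conditional. The route through site preparation does not depend on it.

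**The safeguard sentence is not false.** A reader might infer that the protocol contradicts itself in claiming freedom from physician influence. The sentence covers assignment only, and the locked drawer supports it. It does not reach the later steps, which is a gap and not a contradiction.

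**The surgeon's unblinding is inferred.** The protocol mentions a numbered envelope for each tooth and does not say whether the implant is handed over open or sealed. That is fair. Even so, the implants differ in form, handover precedes surgery and no concealment from the surgeon is stated, so the inference is a strong one.

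**The numbers are assumed and may be small.** This also stands. With one or two teeth lost and a weak link between prognosis and outcome, type I error barely moves.

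**Conclusion.** The point holds as a correctable weakness in timing. The protocol places disclosure before the operation, states no blinding of the surgeon and excludes untreated teeth. Knowledge of the arm can therefore affect site preparation and, if any decision not to proceed is made at surgery, which teeth are analysed.

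The size is unknown. The shifts of 0.05 and 0.11 SD rest on an assumed number of losses, all in one arm, an assumed 1 SD deficit, and teeth treated as independent although about 10 patients would supply one to each arm. Unequal site preparation is not quantified at all.

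A reader might infer that later disclosure would remove the problem at no cost. The documents do not support that. With blocks of 2 and opposite assignment of second teeth, up to 20 of 40 teeth stay predictable, or about 10 if both sites are prepared first. Later disclosure also leaves untouched what the surgeon does afterwards and the teeth lost before surgery. It reduces the bias, at a small cost.

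**What to change.** In Study Design, state that:
- Investigator 4 keeps the assigned implant concealed until the surgeon has recorded that the site is prepared and ready for the graft. For a two-tooth patient this means all study sites in that session.
- The time of disclosure is logged.

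In Statistics, state that every tooth past that point is analysed as randomized, and that randomized teeth left untreated are reported by arm with reasons. That report also makes visible the losses before surgery, which the change in timing cannot prevent.

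The cost is a few sentences of procedure, plus having Investigator 4 available during surgery with the assigned implant concealed. A second implant is not needed. Since the transplants are already prepared for immediate use and Investigator 4 already hands them over, the change is mainly one of timing.

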***Study Products***

Bio-Oss® and Bio-Guide® (Geistlich Pharma AG, Volhusen, Switzerland) and PDL cell sheets (cells obtained from a patient’s tooth/teeth; see inclusion criteria) will be produced at the Research and Development Center for Tissue Engineering (Fourth Military Medical University, [name]) using a standardized procedure (see section 5.1. cell products). Both transplants (Bio-oss® only or Bio-oss®/cell sheets) will be prepared (ready for immediate use) by the laboratory researchers, and Investigator 3, who will perform the follow-up study, will remain blinded to the treatment conditions.

***Duration of the Study***

This clinical trial, including the recruitment of subjects, will be performed from June 1, 2011 to December 30, 2013, and the study is anticipated to finish at the end of 2014.

[figure not shown]

**Figure 1**. Flow chart of the trial describing the selection, randomization, treatment and the follow-up process that will be completed by the clinician (Investigator 3).

**Patients and enrolment**

Patients with periodontitis visiting our dental institution will be requested to participate. This study will be conducted in compliance with Good Clinical Practice guidelines. Prospective patients who provide written informed consent will undergo clinical inspection and an oral cavity diagnosis. We will then select approximately 30 patients (approximately 40 testing teeth) who satisfy the selection and exclusion criteria described below (most of these criteria were chosen from previous similar periodontal clinical trials [34,35]).

***Inclusion criteria***

- those 18 years old and <65 years old;
- those diagnosed with a 2- or 3-walled vertical intrabony defect 3 mm deep from the top of the remaining alveolar bone from radiography and clinical periodontal parameters;
- those who have accomplished the initial preparation and shown good compliance;
- those with a mobility of Degree 2 or less for the tooth under investigation and with a width of the attached gingiva for which the existing GTR and bone graft implantation treatments are considered appropriate;
- those for whom supportive periodontal treatment is applicable (the tooth has the potential to be maintained for at least 3 years) and in accordance with the usual post-operative procedures following flap operation and GTR treatment;
- those whose oral hygiene is well established and who are able to perform appropriate tooth brushing and cleaning following instructions from the investigators and/or sub-investigators after investigational drug administration;
- those who have at least one tooth (e.g., wisdom tooth) that needs to be extracted due to impacted or non-functional reasons and who agree to the tooth extraction;
- those who understand the purposes of the trial and are capable of making an independent decision to comply with trial requirements.

***Exclusion criteria***

- those who took a calcium antagonist during the 4 weeks prior to surgery;
- those in need of the administration of adrenal cortical steroids (equivalent to >20 mg/day of Predonin) within 4 weeks after the surgery;
- those scheduled to undergo a surgical operation in the vicinity of the tooth to be investigated within 36 weeks after surgery;
- those with coexisting mental or consciousness disorders;
- those with coexisting malignant tumors or history of the same;
- those with coexisting diabetes (HbA1C >6.5%);
- those in extremely poor nutritional condition (serum albumin concentration <2 g/dL);
- those with 200 mL of blood drawn during the 4 weeks prior to surgery;
- those given another investigational drug during the 24 h preceding our investigational drug administration;
- those with a coexisting disorder of the kidney, liver, blood and/or circulatory system (Grade 2 or above);
- those who are either pregnant, possibly pregnant or breast-feeding or who hope to become pregnant during the trial period;
- those with a previous history of hypersensitivity to any biologically active drugs;
- those who smoked more than 10 cigarettes during the past 3 months;
- those who are involved with the research team of this trial;
- those with any other condition, as determined by the investigators or sub-investigators, that could make the subject unsuitable for the trial, impair the validity of the informed consent, or impair the subject's suitability for the trial.

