**Fourth Military Medical University**

**2011.06**

**Abstract**

**Background**: Periodontitis, which progressively destroys tooth-supporting structures, is one of the most widespread infectious diseases and the leading cause of tooth loss in adults. Evidence from animal studies indicates that stem cells derived from either bone marrow or the periodontal ligament (PDL) can be used in therapies for the regeneration of lost or damaged periodontal tissues. The aim of this clinical trial is to identify the safety of the clinical use of stem cells in periodontal therapy and to verify whether stem cells in combination with Bio-oss® are more effective than Bio-oss® alone in guided tissue regeneration (GTR) techniques for treating periodontal disease in human patients.

**Methods/Design**: In this protocol, we designed a single-center randomized trial to treat periodontal disease using GTR techniques and bovine-derived bone mineral (BDBM, Bio-oss®) with or without the incorporation of autologous periodontal ligament stem cells (PDLSCs). In total, approximately 30 periodontitis patients aged 18 to 65 years with a total of approximately 40 test teeth with periodontal intrabony defects and who satisfy our selection and exclusion criteria will be enrolled. These patients will be randomly assigned to either the Cell testing group (treatment with GTR and PDLSC sheets in combination with Bio-oss®) or the Control group (treatment with GTR and Bio-oss® without containing cells). During a 12-month follow-up, we will examine the extent of any adverse events related to the use of PDL cells. Moreover, the primary outcome is the magnitude of change in the alveolar bone height, and the secondary outcome measures are improvements in clinical attachment level (CAL), probing depth (PD), and gingival recession (GR).

**Discussion**: The results of this trial will assess the efficacy, safety and feasibility of using autologous PDLSCs to treat periodontal intrabony defects, and these data will provide primary clinical evidence for the future use of autologous stem cells in regenerative periodontal therapy.

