***Evaluation of adverse events***

The investigators will record any adverse event with the exact name, onset date, severity, provided treatment and date of disappearance.

Each adverse event will be graded for severity using the following scale and criteria as outlined by the Ministry of Health and Welfare of the Chinese Government.

- **Mild**: The subject can continue the subsequent schedule without any treatment.
- **Moderate**: The subject can continue the subsequent schedule with treatment.
- **Severe**: The subject cannot continue the subsequent schedule.

The investigators will determine the relationship of the adverse event and the investigational cells.

The investigators will determine whether or not the adverse event is classified as a serious adverse event. A serious adverse event is defined as any experience suggesting a significant hazard, contraindication, side effect, or precaution. A serious adverse event includes any adverse experience resulting in any of the following outcomes:

- Death
- A life-threatening adverse experience
- Impatient hospitalization or prolongation of existing hospitalization
- A disability/incapacity that may interfere with the subject's daily life
- An adverse experience leading to a disability/incapacity
- A serious adverse experience at the same level as the above conditions
- A congenital anomaly/birth

**Efficacy assessment** [34,35]

The main outcome measure in the study protocol is change in the alveolar bone height at 3, 6, and 12 months post-operation. We set the rate of increase in alveolar bone height as the most statistically important outcome (primary outcome). The clinical attachment level (CAL), probing depth (PD), and gingival recession (GR) are generally used to assess pathology in periodontal disease. These parameters do not directly assess the efficacy of cells in periodontal tissue regeneration and were selected in the present study as secondary outcome measures to ascertain whether cells would cause abnormal periodontal healing following periodontal surgery. These measurements will be recorded at baseline and 12-months post-surgery.

***Standardized radiography and dental CT for regions of investigation*** [34,35]

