Our geometrically standardized radiography employs dental film (Kodak InSight Super Poly-Soft; Eastman Kodak Company, New York, USA) and photograph indicators (Cone Indicator-II; Hanshin Technical Laboratory, Hyogo, Japan) that are customized with resin stents. Two doctors specializing in dental radiology from the Department of Oral Diagnosis at Fourth Military Medical University School of Stomatology will measure the changes in the alveolar bone height (%) using the methods described below (Figure 2). Each examiner blinded to the treatment conditions will independently measure this value, and the median of 2 measurements taken from the same image will be selected for analysis. In addition, a dental CT that reports data automatically will be used to assess bone regeneration in selected cases. These data will be used for information purposes only or as a reference for the design of subsequent trials (not included in the analysis of this trial).

[figure not shown]

**Figure 2**. Schematic illustration of the bone regeneration assessment using standardized radiography. Points C, A and B represent the cementoenamel junction, apex and bottom of the bone defect, respectively. The examiner measured the tooth axis heights between Points C and A and between Points C and B (bone-defect depth, BDD) on the X-ray for each patient. To adjust for slight errors due to imaging, the measurements from 5 examiners were multiplied by the A-C ratio of the before to after administration to correct for C-B after administration. Based on C-B data before surgery and during follow-up (3, 6 and 12 months), increse of BDD was calculated to serve as an indicator of increase in alveolar bone height post-operation [37,38].

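### The exclusion for surgery already scheduled near the test tooth ends at 36 weeks, about 16 weeks before the 12-month bone-height film and the only post-operative CAL, PD and GR reading

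*Protocol*

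**What the plan says.** The Protocol's Exclusion criteria list "those scheduled to undergo a surgical operation in the vicinity of the tooth to be investigated within 36 weeks after surgery". This is the only criterion that deals with a further operation close to the study site.

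The assessment times are given under Efficacy assessment. For the primary outcome: "The main outcome measure in the study protocol is change in the alveolar bone height at 3, 6, and 12 months post-operation". The Figure 2 legend gives the same three follow-up times for the films. For CAL, PD and GR: "These measurements will be recorded at baseline and 12-months post-surgery". The Abstract likewise describes a 12-month follow-up.

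Two other places bear on the point. The Exclusion criteria end with a general clause for "those with any other condition, as determined by the investigators or sub-investigators, that could make the subject unsuitable for the trial"; it names neither surgery nor a period. Patients and enrolment says of the criteria that "most of these criteria were chosen from previous similar periodontal clinical trials [34,35".

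**The concern.** The evident purpose of the criterion is to keep a second, unrelated operation from disturbing the site whose bone and attachment are being measured. For that, the window has to run at least to the last measurement, and it does not. Someone with an operation beside the test tooth already scheduled for, say, week 40 is not removed by this criterion. The 12-month film and probing of that tooth could then show the combined result of the trial procedure and the later one.

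What is at stake is the last of the three primary films and the only post-operative reading of each of the three secondary outcomes. In a trial of about 40 teeth, a few such readings carry visible weight.

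**Working it through.** The Protocol gives no figure of its own to reproduce here. The check is calendar arithmetic on its stated times.

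**Inputs**
- Exclusion window: 36 weeks after surgery (Exclusion criteria).
- Bone-height films: 3, 6 and 12 months (Efficacy assessment; Figure 2 legend).
- CAL, PD and GR: baseline and 12 months (Efficacy assessment).
- Planned size: about 40 teeth (Patients and enrolment). About 20 per group is an assumption of near-equal allocation.
- Trial surgery follows the pre-surgical treatments by 4 to 5 weeks (Study Design).
- Convention: 1 year = 365.25 days, so 1 month = 365.25 / 12 = 30.44 days.

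**Length of the gap**
- Window: 36 × 7 = 252 days; 252 / 30.44 = 8.3 months.
- Follow-up: 365.25 / 7 = 52.2 weeks.
- Gap: 52.2 − 36 = 16.2 weeks, or 12 − 8.3 = 3.7 months.
- Share of calendar follow-up: 16.2 / 52.2 = 31%.

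**Which readings fall inside the window**

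| Reading | Week | Within 36 weeks? |
|---|---|---|
| Film, 3 months | 13.0 | Yes |
| Film, 6 months | 26.1 | Yes |
| Film, 12 months | 52.2 | No |
| CAL, PD, GR, 12 months | 52.2 | No |

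One of three post-operative films is outside the window. For CAL, PD and GR, the one post-operative reading is outside.

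**Who could slip through**
The criterion concerns surgery already scheduled when eligibility is checked. Eligibility is re-checked around the pre-surgical treatments. Counting from there, an operation falling in the gap would have to be planned about 36 + 4 = 40 to 52.2 + 5 = 57 weeks ahead. That is a narrow group, and the Protocol does not say how large it is.

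**Weight of one tooth**
With about 20 teeth per group, one affected tooth is 1 / 20 = 5% of its group, two are 10% and three are 15%. No shift in the group mean is calculated, because the Protocol gives no effect of nearby surgery on bone height.

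**The case against.** The strongest reply is that the exposed group is very small. Few patients will have an operation beside the test tooth scheduled 40 weeks or more ahead, and nothing in the Protocol suggests that they are common. The term for nearness is also undefined and may take in operations that never reach the defect. Surgery not foreseen at enrolment may be the likelier disturbance, and no change to this criterion would touch it. All of this stands, and it keeps the point modest.

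A second reply is that the general unsuitability clause lets an investigator refuse such a patient. That stands only in part. The clause is discretionary, and a specific 36-week limit in the same list may suggest that later surgery is acceptable.

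A reader might go further and infer that the treatment comparison is biased. The documents do not support that. Surgery scheduled before allocation is a baseline characteristic, teeth are randomised, and patients are not told their group. In expectation such surgery adds noise and does not favour either group, although groups of about 20 leave room for chance imbalance.

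A reader might also infer that readings taken after nearby surgery have no planned handling. The Protocol's Statistics section does not mention them, but such handling is commonly placed in a statistical analysis plan, which is not at hand. Its absence from the Protocol is no finding.

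Finally, the 31% is a share of calendar time. It should not be read as 31% of the data being exposed, since two of the three films lie within the window.

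**Conclusion.** The mismatch is real and rests on the Protocol's stated times. The window for scheduled nearby surgery closes about 16 weeks before the 12-month film and before the only post-operative CAL, PD and GR reading, and only a discretionary clause covers the interval.

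The practical size is probably small. The frequency is not given, the exposed group is narrow, and the expected effect is noise, with possible chance imbalance at about 5% of a group per affected tooth (assuming about 20 teeth per group). Whether a given nearby operation would change the readings depends on its site and extent, so the conclusion is only that they could be affected.

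Since most criteria were taken from earlier trials, the 36 weeks may not have been adapted to this trial's follow-up. That is an inference; the Protocol does not say so.

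**What to change.** Reconcile Exclusion criteria with Efficacy assessment and the Figure 2 legend, so that the window for surgery already scheduled near the test tooth reaches the 12-month assessment. This is a one-line change to who may be enrolled, and it would bring the uncovered period from about 16 weeks to none.

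The cost is the loss of an occasional candidate. Prevention at enrolment is also cleaner than a later repair. If a 12-month film were set aside, the last-observation-carried-forward rule in Statistics would substitute the 6-month value. For CAL, PD and GR the stated schedule provides no earlier post-operative reading to carry forward.

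The change would not deal with surgery that becomes necessary after enrolment, and should not be presented as doing so.
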